**Thank you for completing this questionnaire.**

[figure not shown]

**DRAFT****SWOG  
S1200 AROMATASE INHIBITOR USAGE FORM**

Page 1 of 5

SWOG Patient ID  SWOG Study No. S12000 Registration Step 1

Patient Initials \_\_\_\_\_ (L, F M)

Time Period: ☐ 12-week visit ☐ 24-week visit ☐ 52-week visitAssessment Period Start Date:  /  / Assessment Period End Date:  /  / 

Institution/Affiliate \_\_\_\_\_ Physician \_\_\_\_\_

**Instructions:** Document AI usage for the reporting period marked above. Please submit this form within 7 days after each assessment. All dates are **MONTH, DAY, YEAR**. Explain any blank dates or fields in the **Comments** section. Place an ☒ in appropriate boxes.

The patient should complete Pages 2-5 of this form.

**STATUS**Date of Last Contact or Death:  /  /  Vital Status: ☐ Alive ☐ Dead  
(submit Notice of Death)

Has the patient had a cancer recurrence or new cancer diagnosed?

☐ No ☐ Yes (submit S1200 Off Protocol Notice)

Has the patient discontinued all AI therapy, without the intent of switching to a different AI?

☐ No ☐ Yes**Comments:**[figure not shown]

**DRAFT****SWOG  
S1200 AROMATASE INHIBITOR USAGE FORM**

Page 2 of 5

|                                                                                                                                          |                                                                                                                                                                                  |                                                         |
|------------------------------------------------------------------------------------------------------------------------------------------|----------------------------------------------------------------------------------------------------------------------------------------------------------------------------------|---------------------------------------------------------|
| SWOG Patient ID               | SWOG Study No.      | Registration Step  |
| Patient Initials _____ (L, F M)                                                                                                          |                                                                                                                                                                                  |                                                         |
| Time Period:  12-week visit  24-week visit  52-week visit |                                                                                                                                                                                  |                                                         |

**Please answer the following questions about your aromatase inhibitor (hormonal therapy) use. Place an ☒ in the appropriate boxes.**

**I. CURRENT AROMATASE INHIBITOR (HORMONAL THERAPY) USE**

**1. Which of the following aromatase inhibitor therapies are you CURRENTLY taking?**

- ☐ Anastrozole (Arimadex)
- ☐ Letrozole (Femara)
- ☐ Exemestane (Aromasin)
- ☐ None, I stopped taking this kind of medication

**2. When did you take your last pill for this therapy?**   /   /

**3. How many pills have you missed in the past week for this therapy?**   (Please provide one number, not a range.)

*continued on next page*

[figure not shown]

**DRAFT**

SWOG  
S1200 AROMATASE INHIBITOR USAGE FORM

Page 3 of 5

SWOG Patient ID

SWOG Study No. S1200

Registration Step 1

Patient Initials \_\_\_\_\_ (L, F M)

Time Period: ☐ 12-week visit ☐ 24-week visit ☐ 52-week visit

**CURRENT AROMATASE INHIBITOR (HORMONAL THERAPY) USE, *continued***

**4. Have you stopped taking this therapy?**

☐ No (**Go to Part II on Page 4**)

☐ Yes → Please indicate why you stopped (*Mark all that apply*)

☐ Cancer recurred

☐ Cost of the medication

☐ Lost or changed health insurance

☐ Doctor recommendation

☐ Participant choice

☐ Side effects → Indicate which kind of side effects (*Mark all that apply*)

☐ Bone and/or joint pain

☐ Osteoporosis

☐ Thinning of bones

☐ Nausea

☐ Vomiting

☐ Hot flashes

☐ Weakness

☐ Fatigue/tiredness

☐ Headache

☐ Insomnia/trouble sleeping

☐ Dizziness

☐ Drowsiness

☐ High cholesterol

☐ Weight gain

☐ Other, specify: \_\_\_\_\_

**Thank you for completing this questionnaire**

2/9/2012

Draft

[figure not shown]

**DRAFT****SWOG  
S1200 AROMATASE INHIBITOR USAGE FORM**

Page 4 of 5

SWOG Patient ID SWOG Study No. Registration Step 

Patient Initials \_\_\_\_\_ (L, F M)

Time Period: ☐ 12-week visit ☐ 24-week visit ☐ 52-week visit**II. PRIOR AROMATASE INHIBITOR (HORMONAL THERAPY) USE****5. Since your last visit, did you switch the kind of aromatase inhibitor therapy that you are taking from one kind to another?**☐ No (**Go to Part III on Page 5**)☐ Yes → Why did you switch from this therapy? (*Mark all that apply*)☐ Cost of the medication☐ Lost or changed health insurance☐ Doctor recommendation☐ Participant choice☐ Side effects → Indicate which kind of side effects (*Mark all that apply*)☐ Bone and/or joint pain☐ Osteoporosis☐ Thinning of bones☐ Nausea☐ Vomiting☐ Hot flashes☐ Weakness☐ Fatigue/tiredness☐ Headache☐ Insomnia/trouble sleeping☐ Dizziness☐ Drowsiness☐ High cholesterol☐ Weight gain☐ Other, specify: \_\_\_\_\_*continued on next page*

2/9/2012

Draft

[figure not shown]

**DRAFT**

SWOG

**S1200 AROMATASE INHIBITOR USAGE FORM**

Page 5 of 5

SWOG Patient ID

SWOG Study No.

Registration Step

Patient Initials \_\_\_\_\_ (L, F M)

Time Period: ☐ 12-week visit ☐ 24-week visit ☐ 52-week visit

**III. MEDICATION ADHERENCE QUESTIONNAIRE (MAQ)**

6. Do you ever forget to take your aromatase inhibitor (hormonal therapy)?..... ☐ Yes ☐ No
7. Are you careless at times about taking your aromatase inhibitor (hormonal therapy)?..... ☐ Yes ☐ No
8. When you feel better, do you sometimes stop taking your aromatase inhibitor (hormonal therapy)?..... ☐ Yes ☐ No
9. Sometimes, if you feel worse after taking your aromatase inhibitor (hormonal therapy), do you stop taking it?..... ☐ Yes ☐ No

*Medication Adherence Questionnaire (MAQ) Morisky, Green and Levine. Medical Care 1986; 24(1): 67-74.*

**Thank you for completing this questionnaire**

Draft

2/9/2012

[figure not shown]

**DRAFT****SWOG  
S1200 FUNCTIONAL TESTING**

Page 1 of 1

SWOG Patient ID SWOG Study No. Registration Step 

Patient Initials \_\_\_\_\_ (L, F M)

Assessment Date:  /  / Planned Assessment: ☐ Baseline ☐ 6-week visit ☐ 12-week visit ☐ 24-week visit ☐ 52-week visit

Institution/Affiliate \_\_\_\_\_ Physician \_\_\_\_\_

**Instructions:** Submit this form at time of registration and at 6 weeks, 12 weeks, 24 weeks, and 52 weeks post-registration. All dates are **MONTH, DAY, YEAR**. Explain any blank fields or blank dates in the **Comments** section. Place an ☒ in appropriate boxes. Circle **AMENDED** items in red and write **AMENDED** across top of form.

**1) Grip strength (kPa):***Between the partially flexed fingers and the palm while the thumb applies counter pressure*

|               | Right                                                         | Left                                                          |
|---------------|----------------------------------------------------------------------|----------------------------------------------------------------------|
| 1st Trial     |   .  kPa |   .  kPa |
| 2nd Trial     |   .  kPa |   .  kPa |
| 3rd Trial     |   .  kPa |   .  kPa |
| Maximum value |   .  kPa |   .  kPa |

NOTE: Ask patient to make 3 maximal voluntary contractions, with 1 minute between each. Give verbal encouragement and record each contraction (in kPa). If these readings are not within <10% of each other, then do further contractions, with 1 minute between each, until they are repeatable. Then record the maximum contraction.

**2) 'Timed Get Up and Go' (seconds):** **Comments:**[figure not shown]

**DRAFT****SWOG  
S1200 ADHERENCE TO ACUPUNCTURE**

Page 1 of 1

|                                                                                                                                                                                                                                                                                                                                                   |                                                                                                                                          |                                                 |
|---------------------------------------------------------------------------------------------------------------------------------------------------------------------------------------------------------------------------------------------------------------------------------------------------------------------------------------------------|------------------------------------------------------------------------------------------------------------------------------------------|-------------------------------------------------|
| SWOG Patient ID                                                                                                                                                                                                                                                                                                        | SWOG Study No.  S  1  2  0  0 | Registration Step  1 |
| Planned assessment:  Registration to 1 week  1-3 weeks  3-6 weeks  6-12 weeks                                                                                                                                                              |                                                                                                                                          |                                                 |
| Patient Initials _____ (L, F M)                                                                                                                                                                                                                                                                                                                   |                                                                                                                                          |                                                 |
| Institution/Affiliate _____ Physician _____                                                                                                                                                                                                                                                                                                       |                                                                                                                                          |                                                 |
| Instructions: Submit this form after 1, 3, 6, and 12 weeks post-registration. All dates are MONTH, DAY, YEAR . Explain any blank dates or fields in the Comments section. Place an  in appropriate boxes. Circle AMENDED items in red and write AMENDED across top of form. |                                                                                                                                          |                                                 |

|                                                                                                                                                                                                                                         |                      |                      |                      |   |                      |                      |                      |                      |
|-----------------------------------------------------------------------------------------------------------------------------------------------------------------------------------------------------------------------------------------|----------------------|----------------------|----------------------|---|----------------------|----------------------|----------------------|----------------------|
| First Acupuncture treatment taken this period:                                                                                                                                                                                   |  | /                    |  | / |  |  |  |  |
| Last Acupuncture treatment taken this period:                                                                                                                                                                                    |  | /                    |  | / |  |  |  |  |
| Maximum number of expected Acupuncture treatments during this period:                                                                                                                                                            |  |  |                      |   |                      |                      |                      |                      |
| Number of completed Acupuncture treatments during this period:                                                                                                                                                                   |  |  |                      |   |                      |                      |                      |                      |
| Number of scheduled Acupuncture treatments that were cancelled during this period:                                                                                                                                               |  |  |                      |   |                      |                      |                      |                      |
| Was Acupuncture interrupted during this period?  Yes  No  N/A                                                                                            |                      |                      |                      |   |                      |                      |                      |                      |
| If Yes, specify date stopped:   /   /        |                      |                      |                      |   |                      |                      |                      |                      |
| Specify reason stopped: _____                                                                                                                                                                                                    |                      |                      |                      |   |                      |                      |                      |                      |
| Was Acupuncture restarted?  Yes  No  N/A                                                                                                                 |                      |                      |                      |   |                      |                      |                      |                      |
| If Yes, specify date restarted:   /   /      |                      |                      |                      |   |                      |                      |                      |                      |
| Specify reason restarted: _____                                                                                                                                                                                                  |                      |                      |                      |   |                      |                      |                      |                      |
| Did the patient receive all required Acupuncture treatments during this period?  Yes  No  N/A                                                            |                      |                      |                      |   |                      |                      |                      |                      |
| If No, specify reason:  Improvement in symptoms  Scheduling difficulties  Other (explain below)                                                          |                      |                      |                      |   |                      |                      |                      |                      |

**Comments:**[figure not shown]

**DRAFT****SWOG  
S1200 ADVERSE EVENT SUMMARY FORM**

Page 1 of 1

SWOG Patient ID  SWOG Study No.  Registration Step Time Period: ☐ Registration to 1-week visit ☐ 1-week visit to 3-week visit ☐ 3-week visit to 6-week visit  
☐ 6-week visit to 12-week visit ☐ 12-week visit to 24-week visit ☐ 24-week visit to 52-week visit

Patient Initials \_\_\_\_\_ (L, F M)

Institution/Affiliate \_\_\_\_\_ Physician \_\_\_\_\_

**Instructions:** Please submit this form at 1 week, 3 weeks, 6 weeks, 12 weeks, 24 weeks, and 52 weeks post-registration.**Document adverse events that occur within the time period marked above. Only document adverse events related to blinded protocol treatment (acupuncture/sham acupuncture) and joint pain/stiffness due to aromatase inhibitor treatment.****Do not document other toxicities related to the aromatase inhibitor treatment.** Document the worst Grade seen during the reporting period. Do not code a condition existing prior to registration as an adverse event unless it worsens. Category lists may not include all adverse events from that category. Record any observed adverse events not listed on the blank lines at the end. All dates are **MONTH, DAY, YEAR**. Explain any blank dates or fields in the **Comments** section. Place an ☒ in appropriate boxes.**ADVERSE EVENTS**Reporting period start date:  /  /  (Day 1 of this Cycle)Reporting period end date:  /  /  (Day one of next cycle. If final cycle, date of first visit or contact after resolution of acute adverse events.)

Were adverse events assessed during this time period?

☐ No ☐ Yes, but no reportable adverse events occurred  
☐ Yes, and reportable adverse events occurred (report below)Date of Most Recent Adverse Event Assessment:  /  / 

| CTC Adverse Event Term                          | CTCAE (4.0)
Grade
(1 - 5) | CTC Adverse
Event
Attribution
Code* | Hospitalization
(at least 24
hours) | CTC Adverse Event Term                                                        | CTCAE (4.0)
Grade
(1 - 5) | CTC Adverse
Event
Attribution
Code* | Hospitalization
(at least 24
hours) |
|-------------------------------------------------|---------------------------------|----------------------------------------------|-------------------------------------------|-------------------------------------------------------------------------------|---------------------------------|----------------------------------------------|-------------------------------------------|
| Arthralgia                                      |             |                          |                       | Syncope                                                                       |             |                          |                       |
| Bruising                                        |             |                          |                       |                                                                               |                                 |                                              |                                           |
| Infections and infestations -
Other, specify |             |                          |                       |                                                                               |                                 |                                              |                                           |
| Joint range of motion
decreased              |             |                          |                       | CTC Adverse Event Term, Other
(specify using CTCAE 4.0 terminology) |             |                          |                       |
| Presyncope                                      |             |                          |                       |                                                                               |             |                          |                       |
| Skin infection                                  |             |                          |                       |                                                                               |             |                          |                       |

\* Attribution codes: 1-unrelated 2-unlikely 3-possible 4-probable 5-definite

**Comments:**

Draft

2/9/2012

[figure not shown]

**DRAFT****SWOG  
S1200 SUPPLEMENTAL AGENTS REPORTING FORM**SWOG Patient ID SWOG Study No. Registration Step 

Patient Initials \_\_\_\_\_ (L, F M)

**Reporting period (select one):** ☐ Baseline ☐ Registration to 1-week visit ☐ 1-week visit to 3-week visit  
☐ 3-week visit to 6-week visit ☐ 6-week visit to 12-week visit ☐ 12-week visit to 16-week contact  
☐ 16-week contact to 20-week contact ☐ 20-week contact to 24-week visit ☐ 24-week visit to 52-week visit

Institution / Affiliate \_\_\_\_\_ Physician \_\_\_\_\_

**Instructions:** Please complete this form at baseline, 1 week, 3 weeks, 6 weeks, 12 weeks, 16 weeks, 20 weeks, 24 weeks and 52 weeks post-registration. Document supplemental agent usage information during the reporting period marked above. NOTE: For the prestudy reporting period, use the date of signed informed consent for reporting period start date and the date of registration for reporting period stop date. All dates are **MONTH, DAY, YEAR**. Explain any blank fields or blank dates in the **Comments** section. Place an ☒ in appropriate boxes.

Reporting period start date:  /  / Reporting period stop date:  /  / **Pain Medications:**

*Please list all pain medications taken during the past week for joint pain or musculoskeletal pain. Also indicate dosage per pill and frequency using the frequency codes below. If "other", specify type and dose units. If more than two "other" medications were taken, explain in comments section. If medications were not taken in pill form, explain in comments.*

|                                                          | Dosage (per pill) | Frequency     |
|----------------------------------------------------------|--------------------------|----------------------|
|  Tylenol (acetaminophen)         |  mg  |  |
|  Ibuprofen (e.g. Motrin)         |  mg  |  |
|  Other NSAID, specify: _____     |  mg  |  |
|  Narcotics (specify in comments) |  mg  |  |
|  Other, specify: _____           |  mg  |  |

**Frequency codes:**

1 = ≤ 1 pill per week  
2 = 2-3 pills per week  
3 = 4-6 pills per week  
4 = 1 pill per day  
5 = > 1 pill per day

*continued on next page*[figure not shown]

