- \_\_\_\_\_ 5.5 Patients must have completed the **S1200** Brief Pain Inventory-Short Form (BPI-SF) (Form #40963) within 14 days prior to registration. Patients must have a worst pain score of at least 5 on the Brief Pain Inventory (item #2) that has started or increased since starting AI therapy.
- \_\_\_\_\_ 5.6 Patients must have a Zubrod performance status of 0 to 1 (see Section 10.3).
- \_\_\_\_\_ 5.7 Patients must not have had prior acupuncture treatment within the past 12 months or for AI-induced joint symptoms at any time.
- \_\_\_\_\_ 5.8 Patients must not have a severe bleeding disorder.

**SWOG Patient No.** \_\_\_\_\_

**Patient's Initials (L, F, M)** \_\_\_\_\_

- \_\_\_\_\_ 5.9 Patients must not have concurrent medical/arthritis disease that could confound or interfere with evaluation of pain or efficacy including: inflammatory arthritis (e.g., rheumatoid arthritis, systemic lupus, spondyloarthropathy, psoriatic arthritis, polymyalgia rheumatica), gout, episodes of acute monoarticular arthritis clinically consistent with pseudogout, Paget's disease affecting the study joint (knees/hands), a history of septic arthritis or avascular necrosis or intra-articular fracture of the study joint, Wilson's disease, hemochromatosis, alkaptonuria, or primary osteochondromatosis.
  
- \_\_\_\_\_ 5.10 Patients must not have a history of bone fracture or surgery of the afflicted knees and/or hands within 6 months prior to registration.
  
- \_\_\_\_\_ 5.11 Patients must not have a history of illness that, in the opinion of the investigator, might confound the results of the study or pose additional risk to the patient.
  
- \_\_\_\_\_ 5.12 Patients must not be on narcotics within 14 days of registration.
  
- \_\_\_\_\_ 5.13 Patients must not have received oral corticosteroids, intramuscular corticosteroids, or intra-articular steroids within 28 days prior to registration.
  
- \_\_\_\_\_ 5.14 Patients must not have received topical analgesics (e.g., capsaicin preparations) or any other analgesics (e.g., opiates, tramadol, with the exception of NSAIDs and acetaminophen) within 14 days prior to registration.
  
- \_\_\_\_\_ 5.15 Patients must not have received or implemented any other medical therapy, alternative therapy or physical therapy for the treatment of joint pain/stiffness within 28 days prior to registration. Therapeutic massage is allowed.
  

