### 10.2 Secondary Endpoints:

To investigate the effects of true acupuncture compared to sham acupuncture and waitlist control on the following outcome measures compared to baseline:

- a. Brief Pain Inventory-Short Form (BPI-SF) worst pain, worst stiffness (items 15 & 16), pain severity, and pain-related interference scores at 6, 12, 16, 20, 24, and 52 weeks.
- b. Western Ontario and McMaster Universities Osteoarthritis (WOMAC) index (pain, stiffness, and function) for the hips and knees at 6, 12, 24, and 52 weeks.
- c. Modified-Score for the Assessment and Quantification of Chronic Rheumatoid Affections of the Hands (M-SACRAH) (pain, stiffness, and function) at 6, 12, 24, and 52 weeks.
- d. PROMIS Pain Impact-Short Form (PROMIS PI-SF) at 6, 12, 24, and 52 weeks.
- e. Quality of life as assessed by the FACT-ES Trial Outcome Index (Version 4) at 6, 12, 24, and 52 weeks.
- f. Functional testing of the hands (grip strength) and legs ('Timed Get Up and Go') at 6, 12, 24, and 52 weeks.
- g. Analgesic and opioid use at 2, 4, 6, 12, 16, 20, 24, and 52 weeks
- h. AI adherence at 12, 24, and 52 weeks.
- i. Urine AI metabolites at 24 and 52 weeks.
- j. Serum hormone biomarkers (estradiol, FSH, LH) and inflammatory biomarkers (serum TNF $\alpha$ , IL-6, IL-12, CRP; urine CTX-II) at 6, 12, and 24 weeks.
- k. Polymorphisms in *CYP19A1*.
- l. Safety and tolerability of acupuncture.

This study will also describe adverse events, assess the association between *CYP19A1* genotype and severity of AI-related joint symptoms, and assess the adequacy of blinding and use of additional off-study acupuncture treatments.

- 10.3 Performance Status: Patients will be graded according to the Zubrod performance status scale.

| POINT | DESCRIPTION                                                                                                                                        |
|--------------|-----------------------------------------------------------------------------------------------------------------------------------------------------------|
| 0            | Fully active, able to carry on all pre-disease performance without restriction.                                                                           |
| 1            | Restricted in physically strenuous activity but ambulatory and able to carry out work of a light or sedentary nature, e.g., light housework, office work. |

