#### Description of Waitlist Control

Patients randomized to the waitlist control group will undergo the scheduled evaluations at baseline, Week 2, Week 4, Week 6, Week 12, Week 24, and Week 52. Patients will be allowed to take acetaminophen and NSAIDs as needed for their joint symptoms, which will be documented as analgesic use at scheduled time points and captured on the **S1200** Supplemental Agents Reporting Form. They must agree not to join any other clinical trial for the treatment of AI-related arthralgias while participating in this study. After the 24-week visit, patients will receive a voucher for 10 free acupuncture sessions to be administered by the study acupuncturist(s) and used off-study at her convenience. Any additional acupuncture treatments received off-study will be recorded at 24 and 52 weeks. All of this information will be recorded on the **S1200** Assessment of Blinding and Additional Acupuncture Form (Form #20574).

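### The pain-medication form has an open top category above one pill a day, so changes in amount that stay above that level are invisible to the analgesic endpoint and to any analgesic sensitivity analysis.

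*Protocol*

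**What the plan says.** Section 10.2g lists the endpoint as "Analgesic and opioid use at 2, 4, 6, 12, 16, 20, 24, and 52 weeks", under a lead-in that sets each secondary outcome against baseline. Sections 7.2 to 7.4 name Form #9413 as the record of pain medication at baseline and at every follow-up contact.

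The pain-medication block of that form (Section 18.0) opens with "Please list all pain medications taken during the past week for joint pain or musculoskeletal pain". It then says "Also indicate dosage per pill and frequency using the frequency codes below". There are five lines: acetaminophen, ibuprofen, other NSAID, narcotics and other. The frequency codes run from one pill or fewer per week, through two weekly bands, to "4 = 1 pill per day" and finally "5 = > 1 pill per day". No field asks for the number of pills or a total dose.

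Two other provisions bear on this. Section 19.1 says of the waitlist arm: "Patients will be allowed to take acetaminophen and NSAIDs as needed for their joint symptoms, which will be documented as analgesic use". Criterion 5.12 says: "Patients must not be on narcotics within 14 days of registration".

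**The concern.** The scale separates light use finely and stops separating at the point where regular multi-dose use begins; two tablets taken once a day already reach the top code. Entry requires a worst pain score of at least 5, and acetaminophen and NSAIDs are the analgesics permitted before registration (criteria 5.5 and 5.14), so use of several pills a day is plausible in this population.

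Two things are at stake. First, a moderate analgesic-sparing effect of acupuncture could be missed on a named secondary endpoint. Second, waitlist patients know their assignment (Section 7.6a). If some of them raise an already daily intake, their worst-pain score may fall and the true-versus-waitlist difference may narrow, and the form would not show the rise. No later analysis plan can repair this, because the amount is never collected.

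**Working it through.** **Plan's own figures.** The protocol gives no power or precision for analgesic use. Its one power statement concerns the primary comparisons. With 52 × 0.9 = 46.8 controls, twice as many on true acupuncture, a difference of 1.7, SD 3.0 and two-sided alpha 0.025, I get 82.2%, against the stated 82%. Nothing below depends on it.

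**Step 1: map pills to codes.** Inputs are the code boundaries on Form #9413. In pills per week: code 1 is 1 or fewer, code 2 is 2–3, code 3 is 4–6, code 4 is 7 (one a day), and code 5 is anything above 7. Drug and mg per pill are held fixed.

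| Change (pills/day) | Pills/week | Code before → after | Recorded? |
|---|---|---|---|
| 8 → 2 | 56 → 14 | 5 → 5 | no |
| 6 → 2 | 42 → 14 | 5 → 5 | no |
| 4 → 2 | 28 → 14 | 5 → 5 | no |
| 2 → 6 | 14 → 42 | 5 → 5 | no |
| 2 → 1 | 14 → 7 | 5 → 4 | yes |
| 2 → 3 a week | 14 → 3 | 5 → 2 | yes |
| 2 → none | 14 → 0 | 5 → unticked | yes |

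The fall from 8 to 2 is (8 − 2)/8 = 75% fewer pills, coded as zero change. A halving is visible from 2 pills a day (2 → 1) but not from 3 or more (3 → 1.5 stays in code 5).

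**Step 2: look for another source of the amount.** BPI-SF item 6 is yes/no on oral medication for joint pain; item 7 is percent relief. Neither gives an amount, and the BPI-SF is not collected at weeks 2 and 4. The comments box on Form #9413 is requested for narcotics, surplus other drugs, non-pill forms and blank fields, not for quantity.

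**Step 3: illustrate the group-level loss.** All inputs here except the arm sizes are assumptions. Evaluable patients are 104 × 0.9 ≈ 94 and 52 × 0.9 ≈ 47. Half take analgesics. Weekly pills are Poisson around a gamma-distributed personal mean (shape 2). The true arm has the stated reduction and the control arm has none. Users are compared by a Wilcoxon rank-sum test at 0.05, with 1,000 simulated trials per row.

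| Mean pills/day | Reduction | Power, counts | Power, codes |
|---|---|---|---|
| 2 | 25% | 29% | 17% |
| 2 | 50% | 88% | 71% |
| 2 | 75% | 99.8% | 99.7% |
| 4 | 25% | 31% | 10% |
| 4 | 50% | 90% | 44% |
| 4 | 75% | 100% | 99% |
| 6 | 25% | 30% | 3% |
| 6 | 50% | 90% | 23% |
| 6 | 75% | 100% | 96% |

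The loss is largest for moderate reductions in heavier users and nearly vanishes for a 75% reduction, because most users then drop out of code 5.

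**The case against.** The strongest reply is that the endpoint is use, not weekly dose, and the form does measure use. It records drug class, strength, an ordinal frequency and whether the drug is taken at all. A rise from none or occasional to daily use, which is a likely form of waitlist escalation, is what the codes capture. Adding a second drug, raising the strength or starting a narcotic also registers. The primary model in Section 11.1 adjusts only for baseline score and site, so no planned primary analysis uses this field. Any waitlist bias of this kind would shrink the true-versus-waitlist difference, so it works against a false-positive claim. The protocol gives no distribution of analgesic use, so the share of patients in the top code is unknown.

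All of that stands, and it limits the point. It does not remove it: a measure of analgesic use compared with baseline ought to register a large change in amount among regular users, and this one cannot if they stay above one pill a day.

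A reader might infer more: that the endpoint can detect no change at all in multi-dose users, that analgesic use cannot be compared with the pain result, or that the opioid part of the endpoint is broken. The documents do not support these readings. Several kinds of change out of code 5 are visible (Step 1), and arms can be compared coarsely on class, strength and code, helped by BPI-SF items 6 and 7. Opioids are excluded at entry, so new use is the natural measure, and the form has a line for it ("Narcotics (specify in comments").

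**Conclusion.** The point holds as a measurement ceiling. For a given drug and strength, any rise or fall that stays above one pill a day is recorded as no change. This limits endpoint 10.2g and any sensitivity analysis of the pain result for differing analgesic use, most of all in the waitlist comparison.

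The code mapping is certain, since it is read directly from the form. The size of the loss is not: it depends on how many patients sit in code 5 and how far their use moves, and the protocol gives neither. On the assumed inputs above, power for a 50% reduction falls from 88% to 71% at a mean of 2 pills a day and from 90% to 23% at 6 a day. Those figures show direction and rough scale only. Priority is minor to moderate: a secondary endpoint and a safeguard on interpretation are affected, and the primary analysis is not.

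**What to change.** In the pain-medication block of Form #9413, replace the frequency code with the number of pills of each drug taken in the past 7 days, or add that number beside the code. Keep mg per pill and the past-week recall the form already uses. Analyse 10.2g as past-week amount (pills × mg per pill) by drug class, compared between arms with baseline taken into account. Opioid use can stay as the proportion with any new use since entry, which the present form already supports.

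The cost is one numeric field per drug on a form still marked as draft, with slightly more recall and data entry at contacts that already take place. It has to be done before patients are assessed on the coded form, since the amount cannot be recovered afterwards.
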